### Relevant concomitant care permitted or prohibited during the trial {11d}

We have not specified any concomitant care to be permitted or prohibited.

### Provisions for post-trial care {30}

There is no provision for post-trial care in the study, and participants will remain under the care of their usual GP.

Pharmacovigilance measures			x	x	x	
Outcome variables						
SARS-CoV-2 infection				x^#^		
Severity of COVID-19 infection ^¤^			x	x	x	
Other variables						
Adherence (spray use)			x	x	x	

*Index cases and infected household members only; ^#^or at the time of symptom development; measured by the time taken for all symptoms to resolve (days), and the number of hospital admissions per group

### Sample size {14}

Our target sample size is a minimum of 124 clusters with at least one uninfected household contact at the baseline to be randomised, assuming an average household size of two [17], an intra-class correlation coefficient (*ICC*) of 0.0170 [18], coefficient of variation (of cluster sizes) 0.50 and a secondary infection rate of 30% [19]. This sample size will allow us to detect if the study spray decreases the relative risk for SARS-CoV-2 infection by at least 50%, with 80% power and alpha = 0.05.

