### Trial design {8}

This is a triple-blind placebo-controlled cluster randomised parallel trial. Clusters, consisting of laboratory-confirmed COVID-19 (index) cases and their household members, will be randomly allocated to each of either the intervention (BioBlock nasal spray) or placebo arms.

A minimum of 124 patients with confirmed COVID-19 (index cases) and their household members will be recruited. Clusters, consisting of an index case and their household members, are randomised (1:1 allocation ratio) to receive application of the BioBlock or to receive placebo spray, both to be administered for 14 days. Participants are contacted on a weekly basis. SARS-CoV-2-infected study subjects are followed up for 21 days to assess symptoms and the course of the disease. Their household members will be tested for SARS-CoV-2 at the baseline and 14-day follow-up and will have exposure information and symptoms recorded. The study will run in two general practitioner (GP) clinics in Tallinn, Estonia.

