### Study population and definitions

The population under investigation consists of the confirmed cases of COVID-19 (irrespective of clinical signs and symptoms) and their close contacts (household members).

For the purpose of this investigation, a household is defined as a group of people living in the same residence. Definition of a household includes two or more people living together in (i) a domestic residence (residential institutions, such as boarding schools, dormitories, hostels or prisons will be excluded) or (ii) a dwelling or group of dwellings with a shared kitchen or common opening onto a shared household space.

Detection of SARS-CoV-2 nucleic acid in a nasopharyngeal specimen will be considered as a confirmed case of COVID-19. COVID-19 cases tested positive within the past 5 days will be considered as newly confirmed [14].

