### Recruitment {15}

Evidence suggests that the most effective method of recruitment by GPs is opportunistic recruitment [20]. GPs are asked to approach all of their consecutive potentially eligible primary care patients (individuals with a positive SARS-CoV-2 RNA test—“index case”) during the episode of care leading to SARC-CoV-2 testing, check for the first set of inclusion and exclusion criteria and, if appropriate, obtain informed consent for study participation. GPs will review study requirements with the index case and potential eligibility of the household member(s) of the index cases and obtain and document consent. Once the index case has consented to the household study, consent procedures will be initiated for the household members of the index. Members of the household of the index may be recruited into the study during the time of initial contact or an agreed upon alternate time within two business days. Study staff will attempt to approach and recruit all members of the household that the index case has shared contact information. If no household members consent to participate in the study, the index participant will still be enrolled and can continue the study activities. If initially uninfected close contacts of index patients contract SARS-CoV-2 infection (that will be detected either at the day 14 visit or due to symptoms at any point of follow-up), s/he will continue the study under the “index case” protocol (use of the allocated spray for 14 days since infection, and follow-up of the course of the disease at days 7, 14 and 21, after infection detection). All follow-up visits (days 7, 14 and 21) will be phone visits.

The setting for this study is a cluster randomised parallel two-arm RCT, with a cluster (the household consisting of the index patient and his/her household contacts) as a randomisation unit. All cluster members (index and his/her close contacts) will follow the same treatment allocation.

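### The 124-cluster target at 80% power needs an average of two analysed contacts per cluster, but the protocol states an average household of two, which includes the index case

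*Protocol article*

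**What the plan says.** The Sample size {14} section of the protocol article gives the target as follows: "Our target sample size is a minimum of 124 clusters", each "with at least one uninfected household contact at the baseline to be randomised, assuming an average household size of two". The other inputs there are an ICC of 0.0170, a coefficient of variation of cluster size of 0.50 and a secondary infection rate of 30%. The claim is that the trial can detect whether the spray "decreases the relative risk for SARS-CoV-2 infection by at least 50%, with 80% power and alpha = 0.05". Statistical methods to handle missing data {20c} makes the test two-sided, and Trial design {8} makes the allocation 1:1.

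Three other places fix what a household and a cluster are and who is analysed:

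- Study population and definitions: a household is the people sharing a residence, and "Definition of a household includes two or more people living together".
- Recruitment {15}: the design has "a cluster (the household consisting of the index patient and his/her household contacts) as a randomisation unit".
- Outcomes {12}: the primary outcome is confirmed infection by day 14 among close contacts. The index case is already infected and cannot contribute.

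On numbers to recruit, Trial design {8} says: "A minimum of 124 patients with confirmed COVID-19 (index cases) and their household members will be recruited". Recruitment {15} adds: "If no household members consent to participate in the study, the index participant will still be enrolled". Statistical methods for primary and secondary outcomes {20a} randomises households before the contacts' infection status is known, and removes from the primary analysis those with no negative contact at baseline.

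**The concern.** In a cluster sample size formula, cluster size means the number of people per cluster who supply the outcome. Here that is uninfected contacts, not residents. If the two in the sample size section is household size under the protocol's own definition, one of the two is the index case and only one person per cluster is analysed. The 124 clusters would then supply about 124 analysed contacts rather than 248.

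What is at stake is the power claim for the primary question. A result that is not significant carries different weight in a trial with 80% power to detect a halving of risk than in one with a little over 50%. A reader cannot tell from the protocol which of these was planned.

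**Working it through.** **Inputs.** From Sample size {14}: control rate p1 = 0.30; 50% relative reduction, so p2 = 0.15; ICC = 0.017; CV = 0.50; 80% power; alpha = 0.05. Two-sided from {20c}. 124 clusters at 1:1 is 62 per arm. Let m be the mean number of analysed contacts per cluster.

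**Step 1: individuals per arm without clustering.** Pooled two-proportion formula, mean rate 0.225:

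n = [1.96 × √(2 × 0.225 × 0.775) + 0.842 × √(0.30 × 0.70 + 0.15 × 0.85)]² / 0.15² = [1.96 × 0.5906 + 0.842 × 0.5809]² / 0.0225 = 120.5.

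**Step 2: reproduce the protocol's figure.** Design effect = 1 + ((CV² + 1) × m − 1) × ICC. At m = 2 this is 1 + (1.25 × 2 − 1) × 0.017 = 1.0255. Clusters per arm = 120.5 × 1.0255 / 2 = 61.8, so 62 per arm and **124 in total**. The match depends a little on rounding: taking n up to 121 first gives 62.04 per arm, hence 126. No other cluster size tried comes close. The same method gives 242 clusters at m = 1 (244 if n is rounded first), 164 at m = 1.5, and 86 at m = 3. Unpooled variance, a continuity correction, or leaving the CV out of the design effect do not bring m = 1, 1.5 or 3 to 124.

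**Step 3: power at 62 clusters per arm for other values of m.** Effective n per arm = 62 × m / design effect, and

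power = Φ{[0.15 × √n_eff − 1.96 × 0.5906] / 0.5809}.

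With one contact in every cluster there is no within-cluster correlation to allow for, so n_eff = 62: (0.15 × 7.874 − 1.1575) / 0.5809 = 0.041, and Φ(0.041) = 0.516. Keeping the formula's design effect of 1.00425 gives 0.515. The detectable relative risk is found by solving the same expression for p2 at 80% power.

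| Analysed contacts per cluster | Power, 30% vs 15% | Relative risk detectable with 80% power |
|---|---|---|
| 1.0 | 52% | 0.34 |
| 1.25 | 61% | 0.39 |
| 1.5 | 68% | 0.44 |
| 2.0 | 80% | 0.50 |

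At m = 1, unpooled variance gives 53% and a t reference 52%. The ICC and CV hardly matter; the loss comes from halving the number of people analysed.

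**Step 4: internal consistency of the inputs.** Every qualifying cluster has an index case and at least one uninfected contact, so at least two people. If the minimum is two and the mean is two, every household has exactly two people and the CV is 0. The stated CV of 0.50 cannot hold together with that mean.

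**Step 5: which clusters make up the 124.** The sample size section counts clusters with an uninfected contact; the design section counts recruited index cases. Index cases with no consenting contact stay enrolled, and clusters with no negative contact are dropped after randomisation, so 124 recruited need not be 124 evaluable. The documents give no rate for this loss. As an illustration only, if 20% of 124 recruited clusters were not evaluable (62 × 0.8 = 49.6 per arm), power would be 43% at one contact and 71% at two.

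**The case against.** The best reply is that the authors meant two contacts per cluster, an average household of three, and that only the label is wrong. Two things favour this. A CV of 0.50 makes sense only if cluster size varies, which suggests that two was entered as the analysed cluster size. And Implementation {16c} and Table 2 prepare five vials per cluster, so larger households are provided for. The cited household-size figure might also include people living alone, in which case eligible households would be larger on average; the documents do not show this. If the mean is two baseline-negative contacts, 124 clusters and 80% power stand.

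This has force against one tempting inference, that the trial's power is 52%. That value holds only at exactly one analysed contact per cluster, and the documents do not establish that. It does not rescue the text: an average of two contacts is stated nowhere, five vials is a supply provision rather than an expected mean, and the wording used is household size.

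A reader might also infer that baseline-positive, under-16 or non-consenting members push the 124 clusters below one contact each. They do not. The target is defined as clusters with at least one uninfected contact, so one per cluster is a floor. Such losses can pull the mean down towards one, but not past it.

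On the recruitment count, it is fair to say that the design section gives 124 as a minimum, that Eligibility criteria {10} asks for at least one further eligible household member, and that the sample size section already has the right definition. What remains is a mismatch between two sections. It is real, but secondary.

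**Conclusion.** The point holds as an error in the stated inputs. The 124 clusters and 80% power require an average of two analysed contacts per cluster; the protocol's stated input, under its own definitions, gives one. Over the range of 1.0 to 2.0 contacts, power to detect 30% versus 15% runs from about 52% to 80%, and the detectable relative risk from about 0.34 to 0.50. Below two contacts the stated power is not reached.

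These figures rest on the protocol's own event rate, effect, ICC and alpha, on the pooled two-proportion formula, and on 124 evaluable clusters. Confidence is high that the stated inputs do not support the stated power. The documents do not settle which value in the range applies. The 20% loss in the recruitment illustration is an assumption.

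**What to change.** In Sample size {14}, replace the household-size input with the expected mean number of baseline-negative, eligible, consenting contacts per cluster, and give a CV for that same quantity. Then restate the power, or the relative risk detectable with 80% power, that 124 clusters provides, and show the range from 1.0 to 2.0 contacts. If two contacts were meant, say so in place of "assuming an average household size of two" and justify the figure. If the mean is nearer one, restating the power makes the protocol accurate but does not restore 80%, which on these inputs would take about 242 clusters.

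As a secondary change, make Trial design {8} agree with Sample size {14}: count towards the 124 only clusters with at least one consenting, baseline-negative contact, and follow index-only enrolments without counting them. Otherwise, restate the power for 124 recruited clusters with an explicit allowance for those that will not be evaluable.

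The cost is rewording two paragraphs and possibly a less favourable stated power. Restating the figures needs no new procedures; counting only evaluable clusters may mean recruiting more than 124 index cases, which the stated minimum already allows.

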### Recruitment {15}

Evidence suggests that the most effective method of recruitment by GPs is opportunistic recruitment [20]. GPs are asked to approach all of their consecutive potentially eligible primary care patients (individuals with a positive SARS-CoV-2 RNA test—“index case”) during the episode of care leading to SARC-CoV-2 testing, check for the first set of inclusion and exclusion criteria and, if appropriate, obtain informed consent for study participation. GPs will review study requirements with the index case and potential eligibility of the household member(s) of the index cases and obtain and document consent. Once the index case has consented to the household study, consent procedures will be initiated for the household members of the index. Members of the household of the index may be recruited into the study during the time of initial contact or an agreed upon alternate time within two business days. Study staff will attempt to approach and recruit all members of the household that the index case has shared contact information. If no household members consent to participate in the study, the index participant will still be enrolled and can continue the study activities. If initially uninfected close contacts of index patients contract SARS-CoV-2 infection (that will be detected either at the day 14 visit or due to symptoms at any point of follow-up), s/he will continue the study under the “index case” protocol (use of the allocated spray for 14 days since infection, and follow-up of the course of the disease at days 7, 14 and 21, after infection detection). All follow-up visits (days 7, 14 and 21) will be phone visits.

The setting for this study is a cluster randomised parallel two-arm RCT, with a cluster (the household consisting of the index patient and his/her household contacts) as a randomisation unit. All cluster members (index and his/her close contacts) will follow the same treatment allocation.

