### Implementation {16c}

Once an index participant has completed baseline assessments, the GP will perform the randomisation utilising the centrally held database. Clusters are assigned to a study group sequentially following the randomisation list, and sprays dispensed by the GP. For each cluster to be randomised, five vials of spray are prepared with a unique serial number. GP clinics will use a courier service to deliver assigned investigational products to participating households. The number of vials delivered to a household will depend on the number of consenting study subjects in the household. The vials also have a dedicated place for user name printing (to individualise spray vials).

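### The target of 124 is counted in index cases in one section and in clusters with an uninfected contact in another, with no allowance for clusters lost in between

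*Protocol article*

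**What the plan says.** Two sections give the same number for different units.

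- Trial design {8}: "A minimum of 124 patients with confirmed COVID-19 (index cases) and their household members will be recruited".
- Sample size {14} reads: "Our target sample size is a minimum of 124 clusters with at least one uninfected household contact at the baseline to be randomised". The stated inputs are an average household size of two, an ICC of 0.0170, a "coefficient of variation (of cluster sizes) 0.50", a secondary infection rate of 30% and a 50% relative reduction, with 80% power and alpha 0.05.

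Three further rules decide which clusters can count.

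- Eligibility criteria {10} asks that the index case has another household member who is eligible. It does not ask that this person has consented.
- Recruitment {15} lets household members join at first contact or within two business days, and adds: "If no household members consent to participate in the study, the index participant will still be enrolled and can continue the study activities".
- Statistical methods {20a} randomises clusters before the contacts' RNA status is known. It then removes clusters with no negative contact from the primary (modified intention-to-treat) analysis.

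On timing, Implementation {16c} says: "Once an index participant has completed baseline assessments, the GP will perform the randomisation utilising the centrally held database".

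**The concern.** The main hypothesis concerns infection in contacts. A cluster with no consenting contact, or whose contacts are all positive at baseline, cannot inform it. The protocol foresees both kinds of cluster, yet one of its two targets counts them and the other does not.

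The sample size wording does not settle this. It describes clusters with an uninfected contact as the clusters to be randomised, but by the protocol's own account that status is unknown at randomisation. The target can therefore only be counted afterwards, and no section says that this will be done or that recruitment runs until the count is met.

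The stated 80% power is at stake. A clinic could meet the Trial design figure in good faith and leave the primary analysis short. A later analysis plan cannot recover clusters that were never recruited.

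**Working it through.** **Inputs.** From Sample size {14}: control risk 0.30; intervention risk 0.15 (50% reduction); ICC 0.0170; coefficient of variation 0.50; cluster size m = 2; power 80%; alpha 0.05. The test is two-sided (Statistical methods to handle missing data {20c}) and allocation is 1:1 (Trial design {8}).

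**Step 1: reproduce 124.** Contacts per arm under independence, with mean risk 0.225:

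n = [1.960 × √(2 × 0.225 × 0.775) + 0.8416 × √(0.30 × 0.70 + 0.15 × 0.85)]² / 0.15²
= [1.1575 + 0.4889]² / 0.0225 = 120.5, rounded up to 121.

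Design effect:

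- without variation in cluster size: 1 + (2 − 1) × 0.017 = 1.017. Clusters per arm = 121 × 1.017 / 2 = 61.5, so 62 per arm and **124 in total**.
- with variation in cluster size: 1 + [(1 + 0.50²) × 2 − 1] × 0.017 = 1.0255. Clusters per arm = 121 × 1.0255 / 2 = 62.04, which is 124 in total before rounding up (126 after).

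The stated figure is therefore the bare requirement for evaluable clusters. Power at exactly 124, with design effect 1.0255, is 80.1%. No inflation is hidden in it.

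**Step 2: power if recruitment closed at 124 index cases.** Let L be the share of clusters without a consenting, PCR-negative contact. The protocol gives no value, so the range below is assumed. Evaluable clusters K = 124 × (1 − L), and effective contacts per arm n = (K / 2) × 2 / 1.0255 = K / 1.0255.

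Power = Φ{[0.15 × √n − 1.1575] / √0.3375}.

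Example, L = 10%: K = 111.6, n = 108.8, and power = Φ[(1.5648 − 1.1575) / 0.5809] = Φ(0.701) = 75.8%.

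| Assumed loss L | Evaluable clusters of 124 | Power | Clusters to randomise to keep 124, i.e. 124 / (1 − L) |
|---|---|---|---|
| 0% | 124 | 80.1% | 124 |
| 5% | 118 | 78.1% | 131 |
| 10% | 112 | 75.8% | 138 |
| 20% | 99 | 70.8% | 155 |
| 30% | 87 | 64.9% | 178 |

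**Step 3: could 124 index cases happen to be enough?** Only if none is lost. At a 5% loss per cluster, the chance that all 124 are evaluable is 0.95^124, about 0.2%.

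**A condition on all of this.** The 124 reproduces only with two at-risk contacts per cluster, and the table assumes that the remaining clusters still average two. If a household of two includes the index case, there is one contact per cluster, and power at 124 clusters is about 52% before any loss. That is a separate question.

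**The case against.** The strongest reply is that both figures are minimums. Nothing in the protocol stops recruitment at 124 index cases, and the only stated end of recruitment is a date, 31 December 2021 (Trial status). The dedicated sample size section already names the right unit, so the Trial design sentence can be read as a loose summary. This stands in part. A reader might infer that the trial cannot reach 124 evaluable clusters, or that the clinics will stop too early, and the protocol says neither. What remains is that it gives two targets, no expected loss and no rule that recruitment closes on evaluable clusters.

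A reader might also infer that index cases are always randomised before any household member has consented. The text does not support that. The schedule in Table 1 places consent at enrolment, ahead of allocation, and Recruitment {15} allows household consent at first contact. Implementation {16c} ties randomisation to the index case's baseline, so it may precede a late household consent but need not. Only the contacts' RNA status is expressly unknown at that point.

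Keeping index cases without a consenting contact also has a purpose. They contribute to the secondary hypothesis on clinical outcomes and to the planned analysis of all randomised patients. Turning them into screen failures would cost information on a stated objective, and the problem does not require it.

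Finally, losses to all-positive households follow from the disclosed decision to randomise before RNA results. Asking for consent earlier would not remove them. That limits which remedy works, but those clusters still need to be allowed for in the target.

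**Conclusion.** The point holds as an inconsistency in the recruitment target with a consequence for power. The number 124 is attached to two units that coincide only with zero loss, while the protocol's own rules create loss, and the figure contains no margin.

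If recruitment closed at 124 index cases, any loss would take power below the stated 80%: about 76% at 10% loss and 65% at 30%. The direction does not depend on the assumed rates, but the size does. The figures assume that loss falls equally on both arms and that the plan's risks, ICC and two contacts per cluster are right. They describe what follows from the Trial design count, and are not a forecast that the trial will stop there.

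**What to change.** 1. In Trial design {8}, replace the count of index cases with the unit used in Sample size {14}.
2. Reword Sample size {14} so that the 124 are clusters with at least one consenting contact who is PCR-negative at baseline, counted once baseline results are in and not at randomisation. Give the expected loss and the resulting number to randomise (for example 138 at 10% or 178 at 30%).
3. Keep a running count of such clusters, pooled over arms and blinded, and close recruitment on it. The laboratory already sends daily results to the clinics and the Coordinating Centre (Specimen collection), and the count uses baseline data only.
4. State in Recruitment {15} that index cases without a consenting contact may stay in for the secondary outcomes but do not count towards the 124.
5. If recruitment must close at 124 index cases or on the stated end date, restate the power for the number of evaluable clusters expected.

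The cost is some rewording, a counter in the database, and a longer randomisation list with matching vial sets. Recruitment may run somewhat longer. If it cannot, the stated power becomes less favourable.
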